## Abstract

**Background:**

People with chronic depression are frequently lost from effective care, with resulting psychological, physical and social morbidity and considerable social and financial societal costs. This randomised controlled trial will evaluate whether regular structured practice nurse reviews lead to better mental health and social outcomes for these patients and will assess the cost-effectiveness of the structured reviews compared to usual care.

The hypothesis is that structured, pro-active care of patients with chronic depression in primary care will lead to a cost-effective improvement in medical and social outcomes when compared with usual general practitioner (GP) care.

**Methods/Design:**

Participants were recruited from 42 general practices throughout the United Kingdom. Eligible participants had to have a history of chronic major depression, recurrent major depression or chronic dsythymia confirmed using the Composite International Diagnostic Interview (CIDI). They also needed to score 14 or above on the Beck Depression Inventory (BDI-II) at recruitment.

Once consented, participants were randomised to treatment as usual from their general practice (controls) or the practice nurse led intervention. The intervention includes a specially prepared education booklet and a comprehensive baseline assessment of participants' mood and any associated physical and psycho-social factors, followed by regular 3 monthly reviews by the nurse over the 2 year study period. At these appointments intervention participants' mood will be reviewed, together with their current pharmacological and psychological treatments and any relevant social factors, with the nurse suggesting possible amendments according to evidence based guidelines. This is a chronic disease management model, similar to that used for other long-term conditions in primary care.

The primary outcome is the BDI-II, measured at baseline and 6 monthly by self-complete postal questionnaire. Secondary outcomes collected by self-complete questionnaire at baseline and 2 years include social functioning, quality of life and data for the economic analyses. Health service data will be collected from GP notes for the 24 months before recruitment and the 24 months of the study.

**Discussion:**

558 participants were recruited, 282 to the intervention and 276 to the control arm. The majority were recruited via practice database searches using relevant READ codes.

**Trial registration:**

ISRCTN36610074

## Background

Major depression is very common, with a UK prevalence at any time of at least 5%, with another 5% having milder episodes [1]. The majority of people with depression in the UK are treated within general practice, it being the third most common reason for consultations [2]. Despite evidence that over half of all patients with an acute depressive episode will have a recurrence, and that the risk of further recurrences increases greatly with further episodes, there appears to be little consistency in the longer-term management of the disorder, and significant psychological, physical and social morbidity in this group [3,4]. In addition, a significant minority of patients (around 18-25%) will have chronic depressive disorders [3]. Chronicity is associated with greater likelihood of psychological, physical and social morbidity, an earlier death from all causes, and the health and social costs are considerable [5,6]. Incomplete recovery increases the risk of relapse and may predict long-term outcome more accurately than baseline severity [7,8]. Evidence also shows that the earlier a recurrence is detected, the better and speedier the recovery, but currently many such patients may be inadequately treated and have little or no specific follow-up in primary care [9,4].

The rationale behind this trial was the treatment of depression as a potentially chronic or recurring problem, using regular pro-active contact and follow-up of at risk patients by practice nurses, supported by general practitioners (GPs) in their practices [10]. There is evidence in favour of such strategies from the USA, but they have not yet been formally researched in the UK [11]. Work from the USA has shown that organised, enhanced care can have a beneficial effect both on the outcomes of patients with acute major depression and also those with a high risk of recurrence [12,13]. However, there is also some evidence that the effect of such a coordinated approach can lapse over time and recent work has indicated that a longer-term approach may be indicated, particularly for those at risk of chronic difficulties [14,15].

The form of organised or enhanced care being trialled has elements in common with the management of other chronic diseases in general practice, such as asthma, diabetes and hypertension [10]. Evidence based guidelines identify similar elements of patient care for a range of chronic conditions, including a well-defined care plan, patient education, scheduled follow-ups, review of outcome and concordance, and targeted use of specialist consultation or referral [16]. Practice nurses are in an excellent position to provide such an approach and there is evidence that they can do this very well, often communicating particularly effectively with patients in the management of chronic problems [17].

## Feasibility Work

A 6-month pilot feasibility study was conducted in three general practices in North London, with 35 patients randomised by practice. The aim was to test out the intervention and the measures to be used in a full trial and to conduct qualitative, in-depth interviews with 12 patients who completed the intervention. Participants responded well to this practice nurse intervention, particularly valuing contact with someone who they perceived as a 'normal, mature person drawing on their own experience', rather than with a mental health professional. Practice nurses had more time than GPs, gave helpful, practical advice and a sense that they were interested in patients' problems [18].

This pilot study demonstrated that it was feasible to recruit sufficient eligible participants willing to take part and that they would be able to complete the relevant questionnaires. The feasibility study also indicated that the chances of contamination between intervention and control patients within a practice was low, as the majority of the patient contact in the intervention was carried out by nurses who were very unlikely have consultations with the control patients to discuss their mental health symptoms, although they might carry out other practice nurse consultations for physical health reasons. We therefore decided to randomise by patient within practices in the main trial, rather than carrying out a cluster randomisation design.

## Methods/Design

This is a randomised controlled trial, with randomisation by patient within practices. The comparison is between 'GP usual care' (control arm), and a 'structured care' approach involving regular follow-up by practice nurses (intervention arm) in addition to GP usual care, for patients with a history of recurrent or chronic depression.

Participants were recruited from 38 general practices which are members of the Medical Research Council's General Practice Research Framework (MRC GPRF), a framework of over 1,000 general practices throughout the United Kingdom. An additional 4 practices were recruited, having received details of the study and expressing an interest in participating (2 from the UK's Primary Care Research Network and 2 from local contacts). See Figure 1 for the distribution of practices nationally.

**Figure 1 F1:**
[figure not shown]
**Location of participating practices**.

Within practices potential trial participants were recruited in the following ways:

• General practitioner and practice nurse recall of potential participants

• Practice database searches by READ code (a clinical classification system widely used in UK primary care) and/or anti-depressant prescriptions [19].

• Practice leaflets and posters in the waiting-room encouraging patients to come forward

For the full inclusion and exclusion criteria see below. This was a pragmatic trial, so we aimed to keep the exclusion criteria to a minimum. Patients who expressed suicidal ideas were not excluded, but the practice nurses were given clear guidelines about their management and at what point it would be appropriate to communicate with the GP if they were concerned about a patient.

### Inclusion criteria

(i) Men and women aged 18 and over

(ii) Two or more documented episodes of depression within the previous 3 years

(These may have been separate episodes with a period of well-being in-between, or a documented history of chronic depression. In either case some treatment, either pharmacological or psychological or both should have been instigated, although it may not have been successful)

(iii) Evidence of recurrent and/or chronic depression via the Composite International Diagnostic Interview [20]

(iv) Baseline Beck Depression Inventory-II score of 14 or above (indicating at least mild depression) [21].

(We selected this inclusion criterion to cover patients with chronic dysthymia and those with residual symptoms from major depression, as there is much evidence that this group is at particular risk of recurrence and poor outcomes)

(v) Sufficient English to be able to complete self-report questionnaires

### Exclusion criteria

(i) Current psychotic symptoms

(ii) Impaired cognitive function

(iii) Incapacitating alcohol or drug dependence

All identified patients were sent a letter from the GP and practice nurse on practice headed notepaper, enclosing a study information leaflet and a reply slip and asking them to indicate whether they would like to meet with the practice research nurse to discuss the study in more detail. Those who declined were asked to give an indication of their reasons for this on the reply slip.

Those who met with the nurse and still wanted to take part after discussing the study were assessed for eligibility using the Composite International Diagnostic Interview (CIDI) questionnaire and given a Beck Depression Inventory (BDI-II) questionnaire to complete [20,21]. Those who fulfilled the inclusion criteria and gave fully informed consent had their details passed to an independent computerised telephone/internet based randomisation centre. The nurse was able to let participants know their randomisation outcome at the baseline interview. All eligible consented participants in both groups were asked to complete the baseline questionnaires in a quiet place in the practice centre before they left, with the aim of achieving a high response rate.

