### Depression-free Days recorded in Mood Diaries

Following successful piloting in the feasibility study all participants were asked to complete regular mood diaries, indicating for each day whether they had been depressed or not. This was something that had been both feasible and acceptable for the six months of the pilot study, but proved overly time-consuming and onerous for many participants in the full trial, with the response rate being quite poor after the first 3 months.

We therefore reduced the requirement to completion of the diaries for 50% of the project time. An algorithm was constructed, with the 2 years of the trial follow-up divided into eight 3 month portions and participants randomly allocated to receiving the diaries for four of these time periods. Random allocation of diary periods means that data can be imputed for the whole trial period and used as a patient record of their depression free days, as well to validate the scores calculated using the BDI-II scores by the method of Lave et al. [25].

The questionnaires listed were self-completed, apart from the CIDI which was administered by the research nurses in the practices, who also collected the service usage data. In order to ensure good response rates, participants were given a booklet with all the self-completion questionnaires to fill in when they attended the surgery at baseline and at 24 months for their assessments.

BDI-II questionnaires and mood diaries during the intervening two years were posted to all participants with a self-addressed envelope enclosed for their reply. A reminder letter and copy of the questionnaire was sent after two weeks if participants did not respond. If they failed to return the primary outcome measure, the BDI-II, they were telephoned by the practice research nurse to prompt them to return the questionnaire.

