### Planned analyses

All data will be double entered, using a reputable data entering service, blind as to participant group.

A description of baseline characteristics will be made between those randomised to the control and intervention groups.

All outcome analyses will include individuals in their randomised arm (intention to treat). Initial descriptive statistics will be used to summarise the differences in outcome between the two groups. We will present means and standard deviations for normally distributed, continuous variables and medians, with inter-quartile ranges, for those not normally distributed. Categorical outcomes will be presented as frequencies and percentages within each of the categories.

Observations at each time point on the same individual will not be independent so a repeated measures generalised linear model approach will be used [32]. This will also allow adjustments to be made for the natural clustering inherent in the study design. Continuous outcomes, which are measured at baseline and at the end of follow-up, will be analysed using analysis of covariance (ANCOVA) to adjust for any differences in baseline values [33]. Results will be presented as adjusted differences in means with 95% confidence intervals and associated p-values. Categorical outcomes will be compared using logistic regression and summarised by comparing the group values of the odds ratios for each outcome using 95% confidence intervals and associated p-values. Statistical techniques will be used to assess the impact of potential missing data [34]. Multiple imputation using a predictive model based approach will be used to impute missing values [35]. No interim or sub-group analyses are planned.

The impact of clustering by GP and/or nurse will be investigated using multi-level modelling. This will ensure that estimated standard errors of the treatment effect will be adjusted for the cluster effects.

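### Baseline WASAS and EQ-5D may have been completed after participants learned their allocation, so the ANCOVA that adjusts for them could introduce bias

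*Protocol article*

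**What the plan says.** The recruitment steps are narrated at the end of the section headed Exclusion criteria. People who met the nurse and wished to take part "were assessed for eligibility using the Composite International Diagnostic Interview (CIDI) questionnaire and given a Beck Depression Inventory (BDI-II) questionnaire to complete". Those who were eligible and consented "had their details passed to an independent computerised telephone/internet based randomisation centre". The next sentence reads: "The nurse was able to let participants know their randomisation outcome at the baseline interview". The one after it reads: "All eligible consented participants in both groups were asked to complete the baseline questionnaires in a quiet place in the practice centre before they left".

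The section Depression-free Days recorded in Mood Diaries adds how the measures were taken: "The questionnaires listed were self-completed, apart from the CIDI which was administered by the research nurses in the practices". It also says that "participants were given a booklet with all the self-completion questionnaires to fill in when they attended the surgery at baseline". Table 1 lists BDI-II, WASAS, CIDI, SAPAS, EQ-5D and CSRI at baseline, and all of these except SAPAS again at 24 months.

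Under Planned analyses, continuous outcomes measured at baseline and at the end of follow-up "will be analysed using analysis of covariance (ANCOVA) to adjust for any differences in baseline values". For costs, the Economic Analysis section names non-parametric techniques and net-benefit regression instead.

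**The concern.** Adjusting for a baseline value is safe in a randomised trial because allocation cannot have influenced it. That holds for anything recorded before randomisation, or before anyone who supplies the answer knows the result. Here the participant supplies the answer and cannot be blinded to the intervention. The article's account allows a depressed patient to hear whether two years of nurse reviews will follow, and then to rate social functioning and quality of life.

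If disappointed controls report a worse state than they otherwise would, or intervention patients a better one, the recorded baselines differ by arm for a reason other than chance. ANCOVA then treats that difference as a chance imbalance and subtracts its share from the 24-month comparison. In that scenario the correction works against the nurse intervention. A shift the other way would flatter it. Randomisation does not remove the error, and more participants do not shrink it. WASAS is the clearest case. EQ-5D falls under the same general ANCOVA rule and also feeds the cost-utility analysis.

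**Working it through.** **Order of steps, set side by side**

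| Step | Where stated | Relation to randomisation |
|---|---|---|
| CIDI and eligibility BDI-II | Exclusion criteria | before |
| Consent, details sent to the randomisation centre | Exclusion criteria | randomisation itself |
| Nurse can tell the participant the result | Exclusion criteria | after |
| Booklet (WASAS, EQ-5D and the other self-report forms) | Exclusion criteria; Mood Diaries section | narrated after disclosure; the only limit is leaving the practice |

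The wording about the booklet refers to the two arms, which fits allocation already existing. The section Randomisation describes an automated 24-hour telephone or internet service, so a result during the visit was feasible. No sentence puts the booklet before disclosure.

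**Which baselines are exposed**

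- BDI-II: inclusion criterion (iv) calls the eligibility score the baseline score, and it precedes randomisation. The booklet is said to hold all the self-completion questionnaires, so a second BDI-II cannot be excluded.
- WASAS and EQ-5D: self-rated, in the booklet, measured at baseline and 24 months, and so within the ANCOVA rule.
- CSRI: three-month recall of service use and productivity losses. ANCOVA is not stated for it, so it is not part of this point.
- SAPAS: exposed in the same way, but baseline only and not an outcome under ANCOVA.

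**Size of a possible bias**

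The plan gives no slope, no shift and no target difference for WASAS or EQ-5D, so there is no figure of its own to reproduce here. (Its 318 for a 4-point BDI-II difference does reproduce, as 2 × 159, but it concerns another outcome.) Everything below is an assumption in SD units.

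The ANCOVA estimate is (y1 − y0) − b(x1 − x0), where b is the within-arm slope of outcome on baseline. If knowledge of allocation makes the recorded baselines differ by d, and no reporting shift is present at 24 months, the bias is −b × d:

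| Slope b | d = 0.1 | d = 0.2 | d = 0.3 |
|---|---|---|---|
| 0.3 | −0.03 | −0.06 | −0.09 |
| 0.5 | −0.05 | −0.10 | −0.15 |
| 0.7 | −0.07 | −0.14 | −0.21 |

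A simulation with 276 and 282 participants and slope 0.5 gave mean biases of −0.002, −0.052, −0.100 and −0.151 for d = 0, 0.1, 0.2 and 0.3.

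**Against the standard error.** With correlation 0.5, SE = √[(1 − 0.25)(1/276 + 1/282)] = 0.073. Biases of 0.05, 0.10 and 0.15 are then 0.68, 1.36 and 2.05 standard errors. With no true effect, a nominal 5% test rejects in about 10%, 28% and 53% of trials (simulated: 12%, 27% and 53%; 5% at d = 0). If only 374 were analysed (67% of 558, the 12-month BDI-II response rate, used for illustration), the figures are about 9%, 20% and 39%.

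**Allowing for a reporting shift at 24 months.** If knowing the arm also moves the 24-month answers by e, the same-scale ANCOVA carries e − b × d. A model using only pre-randomisation covariates carries e. With b = 0.5 and d = 0.2, e = 0 gives −0.10 against 0, while e = 0.10 gives 0 against 0.10. Neither model is always the less biased. The second is free only of the part caused by the baseline.

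**The case against.** The strongest reply is that the order is inferred. The text says what the nurse was able to do, not that it was always done first. The booklet's only stated timing is before leaving the practice, and the mention of both arms may simply be a retrospective label making clear that controls filled it in too. An article also condenses visit procedures. This stands as a limit: the text shows that participants could know their arm, not that they all did. It does not remove the point, because nothing stated protects these baselines and the analysis depends on them.

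Three stronger readings are tempting, and the documents do not support them.

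- A reader might infer that the primary outcome is compromised. The eligibility BDI-II precedes randomisation and is called the baseline score. A second baseline BDI-II is only a possibility.
- A reader might infer that baseline-adjusted costs are biased through the CSRI. The article does not say that ANCOVA is applied to the CSRI, and recalled service use is less open to a change of mood.
- A reader might express the bias as a share of 4/11 = 0.36 SD, the BDI-II effect used for sizing. That belongs to a different outcome. No target effect is given for WASAS or EQ-5D, so such a percentage has no valid denominator.

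It is also fair to object that adjustment need not make matters worse, since shifts at baseline and at 24 months can partly cancel, and that removing the same-scale baseline from the main model gives up certain precision against an unproven bias. Both stand. They are why the remedy below adds an analysis and does not replace one.

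**Conclusion.** The point holds as a possibility that the article leaves open. As narrated, participants could learn their arm before completing the self-report booklet, so the baseline WASAS and EQ-5D used in ANCOVA may be affected by allocation. If they are, the adjusted difference carries about −(slope) × (baseline shift), plus any reporting shift at 24 months.

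The size is unknown. The range of 0.05 to 0.15 SD rests wholly on an assumed slope of 0.5 and assumed shifts of 0.1 to 0.3 SD; with no shift there is no such bias. The exposure is confined to these secondary scales, provided that the eligibility BDI-II is the baseline in the primary analysis.

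**What to change.** Recruitment is complete, so the change is to the analysis wording:

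1. Name the pre-randomisation eligibility BDI-II as the only baseline BDI-II covariate in any model. This has no downside.
2. State whether the booklet was completed before or after disclosure, if records show it.
3. Unless records show that it came before, report for 24-month WASAS and EQ-5D, beside the same-scale ANCOVA, a prespecified analysis adjusting only for variables fixed before randomisation: eligibility BDI-II, CIDI history and practice.
4. Do not claim an effect on either scale that appears only in the model using the post-disclosure baseline.

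The cost is one extra analysis per outcome on data already held, with somewhat lower precision in that analysis. If the same-scale correlation were 0.5 and the pre-randomisation variables explained nothing, its standard error would be √(1/0.75) = 1.15 times that of the same-scale ANCOVA; any correlation of those variables with the outcome reduces the loss. The sample size does not change.

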### Randomisation

We used the MRC computerised telephone randomisation service in Aberdeen, which provides an efficient automated 24-hour service and the choice of randomisation by telephone or Internet in each case. Randomisation was at the patient level within each practice, using a block design to maintain a balance of numbers in the control and intervention groups.

